#### Multimedia Activity Recall for Children and Adults

The Multimedia Activity Recall for Children and Adults [27] is a computerized self-report 24-hour recall tool that allows detailed recording of time use behaviors that has been tested on various populations including adults and those with ME/CFS in a recent study conducted by several of the authors. Some participants with ME/CFS report some cognitive strain and burden completing more than 1 24-hour recall intervention over the telephone at once, so for this study, 4 interviews will be conducted each on separate days (during the week that the accelerometer is being worn) capturing at least 1 weekend and 1 weekday.

#### Height, Weight, and Waist Girth

Weight will be measured using the TANITA BC-418 bioelectrical impedance analysis scale. Participant weight will be taken with participant barefoot and clothed in lightweight clothing only. Height will be measured using the ECOMED seca 284 stadiometer. Two measurements will be taken for both weight and height. If the second weight measurement differs by >1%, a third measurement will be required. Similarly, if the second height measurement is >5 mm different then a third measurement is required. An average of the measurements will be obtained (2 measures) or a median (3 measures). Body mass index (BMI) will be calculated. Waist girth will be measured using an anthropometric tape measure and following standardized protocol by an accredited exercise physiologist.

#### Blood Pressure

Blood pressure will be taken using standard procedures and a sphygmomanometer while participant is sitting or reclining (same position each time). Systolic and diastolic blood pressure will be recorded.

#### Heart Rate Variability

RR intervals will be recorded during 5 minutes of supine rest prior to the exercise test using a personal HR monitor (RS800CX, Polar Electro Oy). RR interval data will be downloaded to Polar Protrainer 5 software (Polar Electro Oy) where artifacts or ectopic heart beats are removed through Polar’s automatic filtering. Data will then be exported to heart rate variability (HRV) analysis software (Kubios HRV Analysis version 2.0 beta 1, The Biomedical Signals Analysis Group) where any remaining artifacts or ectopic heart beats can be removed and the final 2 minutes of recording analyzed for the HRV time domain variable of interest (root mean square of successive differences).

#### Allostatic Load

Blood will be taken after fasting to collect data on insulin and glucose, total cholesterol and high-density lipoprotein (HDL) (so we can calculate low-density lipoprotein [LDL]), C-reactive protein (CRP), and adrenaline and noradrenaline. These measures cover both the primary mediators and secondary outcomes of the AL. Other measures used to calculate AL will include HR variability, BMI, waist girth, and blood pressure.

The AL index will be calculated by determining whether, for each participant, their variables are in the healthy zone (coded 0) or the unhealthy zone (coded 1) and then summed to provide a composite AL index. Some variables will be coded based on clinical cut points; the remaining variables that do not have accepted clinical cut points will be analyzed by calculating the upper 25th percentile (code 1), except HRV where the lowest quartile will indicate risk (code 1). The following criteria will be used to determine the risk zones based on previous studies or published guidelines:

BMI >30 kg/m^2^ = 1Waist circumference >94 cm (men) and >80 cm (women) = 1Fasting lipid profile:Total cholesterol ≥5.2 mmol/L=1HDL <1.00 mmol/L=1LDL ≥3.4 mmol/L=1Fasting glucose >5.5 mmol/L=1Systolic blood pressure ≥140 mm Hg or diastolic blood pressure ≥90 mm Hg = 1CRP >3.00 mg/L (cardiovascular risk cut point) = 1Adrenaline (highest quartile) = 1Noradrenaline (highest quartile) = 1HRV (lowest quartile) = 1

Prescribed medication will be taken into account so that an individual is given the value 1 (indicating health risk) for diastolic and systolic blood pressure if they used blood pressure lowering medication and for HDL cholesterol if they used lipid lowering medication. The maximum value AL=12, minimum=0.

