### Health-Related Outcomes

#### Overview

There will be at least 4 weeks between effort testing and commencement of the intervention with 2 weeks being stable at a pretest pattern of symptoms/activity. Participants may require longer recovery before commencing the intervention.

All health-related outcomes will be measured at 3 time points: baseline, 6 months after baseline at the end of the intervention, and at 6-month follow-up after the intervention has been completed. In addition, accelerometer, inclinometer, and continuous captured HR will be measured during week 6, week 12, and week 18 of the intervention. The Karnofsky Scale [25] will be collected more frequently, with the research assistant recording the Karnofsky Scale value each time telephone contact is made with a participant.

Health-related outcomes have been chosen after extensive consultation with the stakeholder advisory group which included people living with ME/CFS. Outcomes have been selected to first provide data on the primary health-related outcomes (ie, physical activity and allostatic load:11 variables). Outcomes have also been selected to cover client-centered outcomes such as use of time, quality of life, and functioning. These outcomes are of utmost importance to the people with ME/CFS and capture the broader International Classification of Functioning, Disability, and Health framework concepts of activity limitations and participation restriction [26]. Finally, outcomes have been selected to capture the vast range of symptoms reported by people with ME/CFS to ensure the levels are monitored alongside the physical activity changes to ensure safety and investigate net benefit to the participants.

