### Analysis Plan

Exit questionnaires will be audiorecorded, transcribed verbatim, and sent back to participants for member checking. Themes will be extracted and summarized from interview transcripts.

Analysis of continuous data to assess preliminary evidence of benefit will include examination of mean differences and confidence intervals ranging from 75% to 95%. Regression analysis will be used to explore preliminary evidence of a relationship between allostatic load and physical activity. The alpha level will be set at 0.2, an appropriate level for a pilot studies [32]. Categorical questionnaire data will be analyzed using chi-square analysis. As this study is a pilot study, any inferential statistics will be purely exploratory (ie, not powered to detect statistical differences).

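### The allostatic-load medication override covers blood pressure and HDL only, so participants whose total cholesterol, LDL or glucose is controlled by medication are coded 0 on those items

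*Protocol article*

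**What the plan says.** The Allostatic Load section (Methods, Health-Related Outcomes) sets out a full scoring rule. Each variable is coded 0 or 1 by a cut point or a quartile, and the codes are summed. Four items matter here, all in mmol/L and all fasting:

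- total cholesterol, 1 if at least 5.2
- LDL, 1 if at least 3.4
- HDL, 1 if below 1.00
- glucose, 1 if above 5.5

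Drugs enter in one sentence: "Prescribed medication will be taken into account so that an individual is given the value 1". It names two cases. One is "for diastolic and systolic blood pressure if they used blood pressure lowering medication". The other is "for HDL cholesterol if they used lipid lowering medication". Nothing is said for total cholesterol, LDL or glucose, which therefore stay on the measured value. No reason is given for limiting the lipid adjustment to HDL.

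The Overview of Health-Related Outcomes places allostatic load among the primary health-related outcomes, measured at baseline, 6 months and 12 months. The Analysis Plan says: "Regression analysis will be used to explore preliminary evidence of a relationship between allostatic load and physical activity".

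**The concern.** An override of this kind stops treatment from hiding a risk. For blood pressure it does that: the drug lowers the reading, and a high reading is the unhealthy one. Total cholesterol and LDL have the same structure, and so does glucose under a glucose-lowering drug. HDL does not, because its unhealthy direction is low, so bringing lipids down does not move it into the healthy zone. The lipid override is therefore attached to the item where masking is least expected and left off the two where it is direct.

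Two things are at stake. Within a visit, a participant with treated and controlled metabolic risk can look healthier on the index than an untreated participant with the same underlying risk. Across visits, starting a drug can register as a fall in allostatic load that has nothing to do with physical activity.

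**Working it through.** **Index length.** The article states "The maximum value AL=12, minimum=0". Counting the listed criteria gives BMI, waist, total cholesterol, HDL, LDL, glucose, blood pressure (one item joined by *or*), CRP, adrenaline, noradrenaline and HRV, which is 11. That agrees with "physical activity and allostatic load:11 variables" in the Overview but not with 12. Splitting systolic from diastolic pressure, or adding insulin, would give 12. This is a separate matter; here it means only that one point is 1/11 = 9.1% or 1/12 = 8.3% of the scale.

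**Item scoring.** The two rules compared are:

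- *Written*: HDL = 1 if a lipid-lowering drug is used; the other three items as measured.
- *Amended*: total cholesterol = LDL = 1 if a lipid-lowering drug is used; glucose = 1 if a glucose-lowering drug is used; HDL as measured.

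The biomarker values are assumed for illustration. Controlled means total cholesterol 4.5, LDL 2.5 and glucose 5.2. Uncontrolled means 5.8, 3.8 and 6.5. HDL is 1.3 unless stated.

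| Participant | Written (TC+LDL+HDL+glucose) | Amended | Written minus amended |
|---|---|---|---|
| Lipid drug, controlled | 0+0+1+0 = 1 | 1+1+0+0 = 2 | -1 |
| Lipid drug, controlled, HDL below 1.00 | 0+0+1+0 = 1 | 1+1+1+0 = 3 | -2 |
| Glucose drug, controlled | 0+0+0+0 = 0 | 0+0+0+1 = 1 | -1 |
| Both drugs, controlled | 0+0+1+0 = 1 | 1+1+0+1 = 3 | -2 |
| Lipid drug, only LDL controlled | 1+0+1+0 = 2 | 1+1+0+0 = 2 | 0 |
| Both drugs, uncontrolled | 1+1+1+1 = 4 | 1+1+0+1 = 3 | +1 |

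The error therefore depends on whether treatment has taken the value across the cut point. In the last row the forced HDL point makes the written score too high.

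**Change between visits (TC+LDL+HDL).** A participant with raised lipids starts a lipid-lowering drug and becomes controlled. The written rule goes from 1+1+0 = 2 to 0+0+1 = 1, a change of -1. The amended rule stays at 2, a change of 0. With about 10 participants per arm (30/3), one such case moves an arm's mean change by 1/10 = 0.1.

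**Effect on the regression.** The documents supply no rate of medication use, so any figure is conditional. Assume 30 participants, 11 binary items loading 0.6 on a latent risk correlated -0.35 with activity, and allostatic load as the dependent variable. Let the drug-treated shares among those at risk on LDL/glucose be 20/10%, 40/20% and 60/30%. Over 4,000 simulated trials the slope is then flatter by about 4%, 8% and 12%. The mean index is too low by 0.10 to 0.12, 0.21 to 0.24 and 0.31 to 0.36, depending on the assumed item prevalences. The slope's sampling SD is about 64% of its mean, so the shift is 4/64 = 0.06 to 12/64 = 0.19 of one SD. With activity as the dependent variable the same simulation gives a steeper slope, not a flatter one.

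**The case against.** The strongest case on the other side has four parts.

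- **The general principle is inferred.** The article says that medication is considered for two named items; it does not say that every treated risk must count as unhealthy. The criteria are said to rest on earlier studies or guidelines that are not shown, and one point per lipid prescription avoids scoring a single drug twice. It is true that the rule is a convention and not an arithmetic error. But the article gives no reason for choosing HDL, and that choice does not do for lipids what the blood-pressure override does.
- **Treated does not mean scored healthy.** A reader might infer that everyone on these drugs gets 0 on total cholesterol, LDL and glucose. The documents do not support that: treated values beyond the cut points still score 1. A reader might also infer a routine 2-point loss on lipids, but the forced HDL point usually reduces it to 1.
- **The analysis is exploratory.** The trial's primary objective is feasibility and acceptability, and the load-activity relationship is a secondary aim of a pilot. A reader might infer that the slope is pulled toward zero. The article does not say which variable is dependent, and the direction turns on that. This objection stands in full.
- **The amended rule has its own artefact.** A participant with normal lipids who starts a lipid-lowering drug rises by 2 (0+0+0 to 1+1+0), against 1 under the written rule. That is a real cost, of the same kind that the plan already accepts for blood pressure.

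**Conclusion.** The point holds for participants whose total cholesterol, LDL or glucose is on the healthy side of the cut point because of medication. They are coded 0 on those items, and lipid-drug users are coded 1 on HDL regardless of its value. The usual net error is 1 point too low per controlled lipid-treated participant, 2 if measured HDL is below 1.00, and 1 per controlled glucose-treated participant. A false change of -1 can follow the start of a lipid-lowering drug. These sizes take the protocol's handling of blood pressure as the standard and assume that a lipid-lowering drug acts mainly on total cholesterol and LDL.

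The effect on the regression is unknown, because neither the rate of medication use nor the dependent variable is given. Under the assumptions above it is small beside sampling error. The rule is worth correcting because it is stated in full, misdirected for lipids and cheap to change, not because it threatens the pilot's main purpose.

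**What to change.** Reword the medication sentence in the Allostatic Load section so that, at every visit:

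- total cholesterol and LDL are coded 1 for users of lipid-lowering medication
- fasting glucose is coded 1 for users of glucose-lowering medication
- blood pressure is coded 1 for users of blood-pressure-lowering medication, as now
- HDL is scored on its measured value, or the HDL override is kept with a stated reason

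This changes outcome coding only. When the article was published, baseline testing had not begun, so the change could be made before any data were scored. The cost is one sentence, plus recording glucose-lowering drugs alongside the blood-pressure and lipid drugs that the present rule already needs. The downside is that users with low values, or treated for another reason, are scored at risk; the text should say so.

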#### Diet Diary

A pen-and-paper 3-day food diary will be completed capturing all food and drink consumed during the dates including sweets, snacks, nibbles, sauces and dressings, water and supplements (vitamins). The diet data will be analyzed using the FoodWorks software (Xyris).

#### Body Temperature

Body temperature will be measured using an electric thermometer. This will be measured to assess if there is an acute inflammatory response (fever). In addition, participant will also be asked to self-report presence of acute infection during testing periods.

#### Karnofsky Scale

The Karnofsky Scale [25] is used to assess the current abilities of the participant based on a numerical scale from 0 to 100. These scales allow a quick assessment of the participant’s function.

#### Chalder Fatigue Scale

The Chalder Fatigue Scale [28] is one of the most widely used measures for assessing physical and mental symptomatic fatigue experienced by ME/CFS patients. Four response options are available, ranging from “less than usual” to “much more than usual.” The Likert system for scoring was used (0, 1, 2, 3), with a total possible score ranging from 0 to 33. A higher score indicates more fatigue.

#### Cognitive Failure Questionnaire

The Cognitive Failure Questionnaire [29] assesses self-reported deficits in attention, perception, memory, and motor functioning. The questionnaire measures the frequency of everyday cognitive failures or lapses by asking participants to rate how often they make mistakes on a 5-point Likert scale, from 0 (never) to 4 (very often). The instrument produces a global “cognitive complaints” score (ranging from 0-100), with higher scores indicating more cognitive failures.

#### Pittsburgh Sleep Quality Index

The Pittsburgh Sleep Quality Index [30] is commonly used to collect data regarding subjective sleep quality, sleep latency, sleep duration, habitual sleep efficiency, sleep disturbances, use of sleep medication, and daytime dysfunction. The seven component scores are rated from 0 to 3, with 0 being no difficulty and 3 indicating severe difficulty. The composite score of the 7 subscale scores provides a global score ranging from 0 to 21, where higher numbers indicated poorer sleep quality.

#### Short Form 36 Questionnaire

The Short Form Health Survey [31] is a 36-item patient-reported survey of patient health commonly used as a measure of quality of life. The questionnaire was developed at RAND Health as part of the medical Outcomes Study.

#### Cambridge Neuropsychological Test Automated Battery

Cognitive performance will be assessed at each visit using 8 well-validated tests assessing reaction time, attention, memory, and executive function from the Cambridge Cognition, suitable for people living with ME/CFS. Tests include motor training, simple and 5-choice reaction time, spatial working memory, pattern recognition memory immediate and delayed, one touch stockings of Cambridge, attention switching task, and rapid visual processing. The order that tests are delivered has been determined with key experts in cognitive testing at Cambridge Cognition so longer tests are separated with shorter tests. This will ensure adequate breaks between testing occur. All testing is automated on a tablet to reduce administration error between participants. Furthermore, testing will take place in a small quiet clinic room with a bed available if participant needs to lie down and rest for administration or in between tests. Snacks and water will be available to participants throughout the cognitive testing.

### Adverse Events

A comprehensive adverse events reporting protocol has been developed for this study based on the stakeholder group feedback and previous literature. An adverse event (AE) will be defined as “any clinical change, disease, or disorder experienced by the participant during their participation in the trial, whether or not considered related to the intervention studied in the trial.”

AE data will collected (1) during every preplanned phone contact between the participant and the research assistant, (2) if the participant contacts the research assistant to report an AE, and (3) during the 3 testing sessions (baseline, 6 months, and 12 months). Questions will be asked about the following 3 categories to encourage the participant to report AEs: any new comorbid medical conditions reported if not previously reported at baseline, any events for which the participant consulted their general practitioner or other medical advisor or took medication, any other events that might have affected the health status of the participant (eg, increased work stress).

The research assistant will have knowledge of participant allocation (ie, control or active intervention group) and as such will be able to use any AE data reported to provide activity counseling and advice regarding the intervention. If an AE is reported, participants will be asked whether they consider the event to be directly caused by the intervention.

A serious adverse event (SAE) will be defined as one of the following outcomes:

DeathThreat to life (ie, an immediate, not hypothetical, risk of death at the time of the event)Required hospitalization except for elective treatment of a preexisting conditionIncreased severity and persistent disability, defined as (1) severe (ie, significant) deterioration in the participant’s ability to carry out their important activities of daily living (eg, employed person no longer able to work, caregiver no longer able to give care, ambulant participant becoming bed bound) and (2) symptom and disability persistent (ie, of at least 4 weeks continuous duration)Any other important medical condition which, though not included in the above, might require medical or surgical intervention to prevent one of the outcomes listed

For any AE established as serious, a medical specialist member of the stakeholder advisory group will be asked to establish whether or not the event was a serious adverse reaction based on treatment allocation information. A serious adverse reaction will be considered to be a reaction to the trial. Both medical specialist and participant attribution will be reported.

A nonserious adverse event (NSAE) will be any health event that was not categorized as an serious AE or serious adverse reaction. NSAEs will be rated as mild, moderate, or severe by both the participant (at the time of reporting) and a medical specialist. The duration of any increases in severity or disability from these events will also be recorded.

Each NSAE will be ascribed a body system (gastroenterological, neurological, etc) by a health practitioner team member. NSAEs attributed to ME/CFS (ie, considered to be a symptom of ME/CFS) will be put into a separate category. To monitor disability, each time the research assistant calls a participant they will be requested to self-report their disability on the Karnofsky disability scale.

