### Protocol Development

A stakeholder advisory group was convened including 2 representatives from the local state ME/CFS society, a rheumatologist with extensive clinical and research knowledge of ME/CFS, a general physician with extensive clinical expertise in managing ME/CFS, 2 adults currently living with ME/CFS, and the research team. The primary purpose of the stakeholder advisory group was to assist in the consumer-driven and evidence-based development of the final protocol. A 6-month consultative development phase was completed in December 2016. The stakeholder advisory group welcomed and considered comments and concerns from external bodies (eg, national and international support groups).

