### Effort Testing (Baseline Only)

Prior to randomization, participants will be screened for eligibility and will participate in either a maximal effort 2-day testing protocol or a submaximal effort protocol. A submaximal effort protocol has been included as an option as community feedback indicated unwillingness from some people due to the potential symptom flare-up predicted with the maximal protocol.

Effort testing on a bicycle ergometer is required to accurately determine the HR and RPEs at ventilatory threshold (VT) or 10% below the VT for each participant. This 10% below VT has been posited as a preferred limit to stay below to avoid symptom flare-up [23] and will be employed in this study for all 3 arms.

The 2-day maximal effort testing protocol is a smaller study running concurrently at the University of South Australia looking to confirm the differing physiological responses demonstrated by people with ME/CFS due to postexertional malaise during repeat exercise testing when compared to healthy controls. The 2-day maximal effort testing protocol will involve attending the university on 2 consecutive days and participating in the same testing protocol on a cycle ergometer wearing a gas analysis mask. A subjective questionnaire regarding fatigue status will be completed, followed by a 10-minute period of rest while wearing an HR monitor. The incremental exercise test on the bike will progress from very light to maximal exercise over a period of 8 to 12 minutes. The test starts with a 5-minute, 40 watt warm-up, during which rate of HR increase is assessed. Following this 5 minutes, the test increases using a ramp protocol, with increases of 5 watts every 20 seconds (so 15 watts per minute on average). The test finishes when the participant reaches volitional exhaustion. Both testing sessions will be conducted at the same time of day.

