## Results

A 6-month extensive consultative protocol development phase has been completed; 3 comprehensive rounds of protocol topics, comments, and plans for amendment occurred.

The first round focused on the following general topics: inclusion criteria, time frame between effort testing and intervention commencement, time and frequency of assessment, and the inclusion of continuous HR data collection. The Karnofsky Scale and alternative disability scales were discussed. The second round included discussion on the following broad topics: design modification to 3-arm trial, symptom history data collection, and the pacing and physical activity protocol. The third round involved discussion on the following topics: AEs protocol, adherence diary, and clarification of maximal and submaximal effort test procedures.

Virtual meetings allowed for interactive group discussion, and consensus was reached on all aspects of the protocol. All members of the stakeholder advisory group have endorsed the current protocol. Enrollment began in January 2017; as of publication, 12 participants were enrolled. Baseline testing is scheduled to commence in mid-2017.

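### Participants and the specialist attribute serious adverse events to different causes, and the specialist's call is made with the arm known, so the two attributions cannot be compared and by-arm reaction counts are at risk of bias

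*Protocol article*

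**What the plan says.** All of this is in the protocol article. Under Adverse Events, events are recorded whether or not they are thought related, at every scheduled telephone contact, when the participant reports one, and at the three testing sessions, baseline included. When an event is reported, "participants will be asked whether they consider the event to be directly caused by the intervention".

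Serious adverse events are defined by outcome. One criterion is severe loss of function lasting at least 4 weeks. Attribution comes next. Once an event has been classed as serious, one of the advisory group's physicians "will be asked to establish whether or not the event was a serious adverse reaction based on treatment allocation information". The section then adds: "A serious adverse reaction will be considered to be a reaction to the trial". It closes the topic with: "Both medical specialist and participant attribution will be reported".

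Three other sections bear on this:

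- **Effort Testing (Baseline Only):** before randomization each participant "will participate in either a maximal effort 2-day testing protocol or a submaximal effort protocol". The submaximal option was added because some people were unwilling to do the maximal test, given the flare-up expected from it.
- **Protocol Development:** the purpose of the advisory group was "to assist in the consumer-driven and evidence-based development of the final protocol".
- **Results:** "All members of the stakeholder advisory group have endorsed the current protocol".

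**The concern.** There are two separate issues.

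The first is an inconsistency of definition. The participant judges *the intervention*, and only direct causation by it. The specialist judges *the trial*. Testing belongs to the trial but not to any assigned program. If the two attributions are reported side by side, a reader cannot tell whether a disagreement reflects a different view of the facts or a different question.

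The second is the basis of the specialist's call. In this illness the hard decision is whether a relapse is a reaction or the natural course. Knowing the arm can tip that decision. It is made by someone whose group helped to shape the protocol and endorsed it.

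The Introduction says that the safety of activity-based programs in this population is disputed and that intervention studies leave the risk of adverse responses to graded exercise unclear. The Conclusion says that this pilot is to guide later effectiveness trials. Its counts of reactions, although descriptive, are therefore likely to be read.

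**Working it through.** The plan gives no figure for serious event rates, no safety margin and no safety test, so there is nothing to reproduce. The check sets the rules side by side and applies them, as written, to the kinds of event that the article makes foreseeable.

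| Event | Participant's question (direct cause by the intervention) | Specialist's question (reaction to the trial) | Does allocation inform the answer? |
|---|---|---|---|
| Severe relapse after the effort test, before randomization | No: no program has been assigned or begun | Yes if testing is part of the trial; no if only the intervention is meant | No: none exists when the event occurs |
| Severe relapse after testing at 6 or 12 months | No, if testing is the cause | Yes or no, on the same ambiguity | Allocation exists but says nothing about testing |
| Severe relapse caused by the assigned program | Yes | Yes | Yes |
| Severe relapse from the natural course | No | No, but this is the call that the arm label can tip | Yes, and it may sway the call |

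The first row is not contrived:

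- Adverse events are collected at baseline testing.
- Randomization follows baseline assessment (Intervention).
- The article allows at least 4 weeks between effort testing and the start of the intervention, and says that some participants may need longer (Health-Related Outcomes, Overview).
- The persistent-disability criterion also requires at least 4 weeks, so a severe and prolonged relapse after testing could meet it.

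**What the specialist's call can change.** Adverse events are recorded regardless of cause. Serious events are defined by outcome and are already classed as serious when the specialist is asked about cause. So the attribution moves only the subset labeled serious adverse reactions. All-cause counts by arm are untouched by it.

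**Sensitivity of that subset.** Inputs: 30 participants (Sample Size) and 1:1:1 allocation (Trial Design).

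- Per arm: 30 / 3 = 10.
- One reclassified participant: 1 / 10 = 10 percentage points, for example 0/10 to 1/10.

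This holds in any arm of 10, masked or not. It shows how much one call weighs. It is not evidence that calls will be wrong.

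**The case against.** The strongest reply has five parts.

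1. **The definition may be mere looseness.** The sentence on reaction to the trial follows directly on one about treatment allocation, so the trial's intervention is a natural reading. This is a fair reading, but not the only one. If it is the intended one, harm from testing is captured by neither rater's question. Either way the wording must be settled.
2. **Judging a reaction requires knowing the exposure.** This stands for the final attribution. It does not rule out a first rating without the arm.
3. **The safeguards are substantial.** All-cause recording, outcome-based seriousness and publication of both attributions are real strengths. They confine the problem to reaction counts. Publishing both attributions helps only if both answer the same question.
4. **The advisory group only assisted.** Correct: the article lists its two physicians apart from the research team and does not say that they designed the trial. The link is assistance and endorsement, which is less than authorship but not independence.
5. **Detail may lie in the separate adverse event protocol, which is not shown.** That could hold form wording. However, the article itself states both referents and the basis of the specialist's call, and those statements do not agree.

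A reader might go further and infer that the between-arm safety comparison is biased. The article does not support that. It plans no between-arm test of reactions and calls all inference exploratory. The label could push the call either way: toward a reaction in an activity arm, or toward excusing one. Nor is the specialist's review the only judgement that could be masked, since a medical specialist also rates the severity of nonserious events.

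**Conclusion.** The point holds in limited form.

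- **Established from the text:** the two raters are given different causes to judge, and the participant's question leaves out harm from study testing. Whether the specialist's question includes it is unclear, and allocation cannot inform a judgement on an event before randomization. As written, the two reported attributions cannot be compared.
- **A risk, not a demonstrated bias:** serious adverse reaction counts by arm, made with allocation known by an assessor who is not fully independent, may be distorted in an unknown direction. One changed call is 10 percentage points in an arm of 10. The number of serious events to expect is not given, so the likely total effect cannot be sized.
- **Not affected by this attribution:** all-cause adverse event and serious adverse event counts.

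This assumes equal arms of 10 and that the unshown adverse event protocol does not already reconcile the two questions. The change is worth making before events accrue, because an attribution collected on one question cannot later be converted to the other.

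**What to change.** 1. Ask the participant and the specialist the same two questions for each event: was it related to study testing, and was it related to the assigned program? For events before randomization only the first applies. State in the definition of a serious adverse reaction which of the two it covers.
2. Have the same specialist rate each event first from a narrative with the arm removed, including the severity of nonserious events. The specialist then gives the final attribution with allocation known. Report both, so that any shift caused by the label is visible.
3. Present all-cause serious adverse events by arm as the main safety summary, with attributed reactions beside it.

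The cost is a revised form, redaction of narratives and a few minutes per event. No extra assessor is needed. Masking will be imperfect, since some narratives will reveal the arm. Keeping the same specialist makes the effect of the label visible but does not make the assessor independent. Urgent care decisions stay unmasked.
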